### Sample size calculation

To date, no exact data on differences in functional outcome (LEFS) between the two different aftercare treatments for patients with fractures of the lower extremities are available. In two studies, the LEFS is expected to be 65 points (SD 10) in the non-weight bearing group [18, 19]. In this study we consider an increase in LEFS of 10% or more in the permissive weight bearing treatment group. In order to detect a difference between two independent means (two groups), assuming that an equal number of patients in both groups will be included, with an alpha of 5% and beta of 20% (power 80%), the sample size should be at least 51 for both groups, thus leading to a total number of 102. Anticipating a 20% drop out and 10% more patients to obtain equal groups, a total of 134 patients have to be recruited.

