### Primary outcome measures

ADL with Lower extremity functional scale (LEFS).

Outcome variables gauging functional outcome:

Score on LEFS [20] at 0, 2, 6, 12 and 26 weeks post-surgery.

LEFS: This is a questionnaire containing 20 questions about a person’s ability to perform everyday tasks. The LEFS can be used by clinicians as a measure of patients’ initial function, ongoing progress and outcome, as well as to set functional goals. The LEFS can be used to evaluate the functional impairment of a patient with a disorder of one or both lower extremities. It can be used to monitor the patient over time and to evaluate the effectiveness of an intervention. The questionnaire’s rating scale consists of 80 points. The lower the score the greater the disability [20].

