### Statistical analyses

Data will be recorded in the digital study database and will be analyzed by a researcher blinded to the study groups the patients entered into.

Variations in case mix between centers can influence the interpretation of outcome data. Therefore, for each of the data sets collected, differences in outcome variable between the services will be tested using multiple MANCOVA’s, entering various indicators of case mix as co-variates (i.e. age, gender, ISS, number of complications, etc).

Insole pressures will be presented as mean ± SD. Statistical analysis of pressures involves repeated-measures two way ANCOVA using time as the within-group factor and treatment protocol as the between-group factor. Post-hoc group comparison at the different time points is only performed when the overall repeated-measures tests are statistically significant. A Bonferroni approach will be used to avoid spurious false positive findings. All scores will be tested for normality using the Shapiro-Wilk test. Multilevel factor analysis will be performed to determine independent factors related to the primary outcome parameter functional outcome.

Statistical analysis will be performed using the Statistical Package for Social Sciences (SPSS, IBM), version 23. Level of significance will be set at alpha< 0.05.

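### The stated 51 per group does not follow from the stated inputs, which give 39 at 80% power; 51 gives about 90% power

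*Protocol article*

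**What the plan says.** All the planning figures stand in the protocol article under Sample size calculation.

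- Control group: "the LEFS is expected to be 65 points (SD 10) in the non-weight bearing group". No SD is given for the permissive weight bearing group.
- Effect: "we consider an increase in LEFS of 10% or more in the permissive weight bearing treatment group". The target is not given in points.
- Test and error rates: "In order to detect a difference between two independent means (two groups", with equal groups, and "with an alpha of 5% and beta of 20% (power 80"%. Sidedness is not stated here. The Statistical analyses section sets a 0.05 significance level and does not state it either.
- Result: "the sample size should be at least 51 for both groups, thus leading to a total number of 102".
- Recruitment: "Anticipating a 20% drop out and 10% more patients to obtain equal groups, a total of 134 patients have to be recruited".

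Under Primary outcome measures, the article also says of the LEFS: "The questionnaire’s rating scale consists of 80 points". This matters only if the 10% is read as a share of the scale.

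**The concern.** The article prints nearly every input to a two-sample comparison of means and also prints the answer, so a reader can check one against the other. They disagree by 12 patients per group (51 against 39), or 31%, which is too much for rounding or a choice of formula. At least one element behind 51 is therefore missing or misreported: the power, the sidedness, the alpha, the difference or an SD. This is the sizing of the primary outcome, and as written the reader cannot tell what effect the study was designed to detect or with what power.

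The step from 102 to 134 raises a smaller question: whether it delivers both the allowance for dropout and the reserve for equal groups that the text names.

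**Working it through.** **Inputs.** From Sample size calculation: control mean 65, SD 10, increase 10%, alpha 0.05, power 0.80, ratio 1:1. Assumed because not stated: SD 10 in the permissive group too, and a two-sided test (one-sided also tried).

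**Difference.** 0.10 × 65 = 6.5 points; d = 6.5/10 = 0.65.

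**Trying to reproduce 51.** Normal approximation: n per group = 2(z₁₋α/₂ + z₁₋β)²/d².

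- Two-sided, 80% power: 2 × (1.960 + 0.842)²/0.65² = 37.2, so 38. The exact noncentral-t calculation gives 38.1, so **39 per group, 78 in total**.
- One-sided, 80% power: noncentral-t 29.97, so 30.
- 10% read as 10% of the 80-point scale: 8 points, d = 0.80, noncentral-t 25.5, so 26.
- Rank-test correction of the two-sided figure: 38.1/0.955 = 39.9, so 40; with the worst-case efficiency, 38.1/0.864 = 44.1, so 45.

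None of these gives 51.

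**What does give 51.** Each route changes or adds an input:

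| Route to 51 | Noncentral-t n | Departure from the text |
|---|---|---|
| d = 0.65, two-sided 5%, power 90% | 50.7 | power stated as 80% |
| d = 0.50, one-sided 5%, power 80% | 50.2 | 5 points and one-sidedness not stated |
| d = 0.65, two-sided alpha 0.0167, power 80% | 51.0 | alpha stated as 5% |
| 6.5 points, SD 10 and 13, two-sided 5%, power 80% | 50.95 | SD 13 not stated |

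In the last row the root-mean-square SD is √((100 + 169)/2) = 11.6, so d = 6.5/11.6 = 0.56.

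**Power of 51 per group on the stated inputs.** d = 0.65, two-sided 5%: 90.2% by noncentral-t (90.7% by normal approximation). At 39 per group it is 80.9%.

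**The recruitment figure.** 134 can be reproduced by multiplication: 51 × 1.3 = 66.3, so 67 per group and 67 × 2 = 134; or 102 × 1.2 × 1.1 = 134.6.

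- After 20% dropout: 134 × 0.8 = 107.2, so 107 completers, above 102. Dropout alone needs 102/0.8 = 127.5, so 128.
- Reserve left: 107/102 = 1.05, about 5%.
- Both allowances in full: 102/0.8 + 0.10 × 102 = 137.7, so 138; or 102/0.8 × 1.1 = 140.25, so 141. The gap is 4 to 7 patients.
- If 107 completers split 60/40 (64.2 and 42.8), the effective size per group is 2 × 64.2 × 42.8/107 = 51.4, still above 51. Power for 6.5 points is then about 90%.

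**The case against.** **The error is on the safe side.** On the stated inputs 51 exceeds 39, and the text presents 51 as a minimum. This stands, and it is why the point is a reporting error and not a design fault.

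**39 rests on an equal-SD assumption.** The SD of 10 is given for the control group only, and an SD of 13 in the permissive group would give 51. This also stands. It means that the review cannot say which input went wrong, and that the author must supply it. It does not rescue the text, because a reader given one SD will use it for both groups.

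**A reader might infer that the study is underpowered.** With d = 0.50 and a one-sided test behind 51, a two-sided 5% test at 51 per group would have 71% power. The documents do not support this. They state neither a 5-point target nor a one-sided test. The directional wording of Hypothesis 1 leaves a one-sided calculation possible but is no evidence that one was done.

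**A reader might infer that 134 is simply wrong.** Taking 20% off 134 and then a further 10% leaves 96, below 102. That treats the 10% as a second loss. The article describes it as extra recruitment to obtain equal groups, and surplus patients in the larger group would still be analysed. The figure follows from ordinary multiplication and covers the dropout. Only the size of the remaining reserve differs from the text.

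**An article may leave the inflation formula to the full protocol.** Fair, and the reason the 134 point is secondary. The argument does not extend to 51, where the article prints both the inputs and a result that they do not produce.

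**Conclusion.** The point holds for 51 per group. The stated inputs give 39 per group (two-sided, SD 10 in both groups) or 30 (one-sided). At 51 per group, power for 6.5 points is about 90%, against the stated 80%. This assumes a two-sample t-test on the LEFS and takes no account of clustering by hospital, which is a separate matter. The documents do not show which input differs from the one actually used.

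For 134 only a minor remark holds: it leaves a reserve of about 5% over 102 after 20% dropout, where the text implies 10%.

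Severity: moderate reporting error, conservative on the stated inputs.

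**What to change.** 1. State the sidedness, the target difference in LEFS points, the SD assumed in each group and the power used, so that 51 can be reproduced.
2. If that cannot be done, correct the text in one of two ways: 39 per group (78 in total) for 80% power; or 51 per group kept, with about 90% power for 6.5 points stated (two-sided 5%, SD 10 in both groups, before any hospital clustering).
3. If 102 evaluable patients are kept, say how 134 was obtained and what it delivers: 107 completers after 20% dropout and about 5% in reserve. To keep both allowances in full, the target would be 138 (reserve as 10% of 102) or 141 (reserve multiplied).

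The cost is a few sentences. Neither 51 nor 134 has to change if the text states what each provides.

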### Interventions

#### Permissive weight bearing

Instead of prescribing a rigorous regime of non-weight bearing, patients are instructed and trained to start weight bearing as tolerated. The limitation in weight bearing is only dependent on the patient’s perception of pain, feeling of instability, or redness and swelling at the site of the fracture. In therapy sessions the physiotherapists stimulate early weight bearing and instruct patients to perform exercises to achieve more weight bearing when tolerated. The goal of the protocol is not to achieve full weight bearing as quickly as possible, but rather to stimulate the patient to increase weight bearing depending on his ability to do so, while maintaining a safety margin to avoid complications or to detect complications early.

Non-weight bearing or restricted weight bearing (current guidelines or AO-guideline):

The standard aftercare treatment in surgically treated trauma patients with (peri)- or intra-articular fractures of the lower extremities is non-weight bearing or partial weight bearing [3]. According to the AO-protocol, postoperative management of (peri)- or intra-articular fractures of the lower extremities consists of non-weight bearing for 6–12 weeks followed by partial weight bearing with a 25% increase in weight loading every week [1]. Non-weight bearing is taught as per the institutional standard, based on the prescribed aftercare treatment. Insole pressure measurement system will be used to monitor the weight bearing and the compliance of the patients (see below).

### Data collection

Baseline measurements will be performed as soon as possible post-injury (= week 0). Further measurements will be taken at week 2, week 6, week 12 and week 26 post trauma (see also flow chart, Fig. 1).

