### Population

Trauma patients, aged 18 years or older, with a surgically treated fracture of the pelvis/acetabulum or a surgically treated (peri)- or intra-articular fracture of the lower extremities, where, according to the current guidelines, permissive weight bearing would not be allowed in the first weeks post-operatively, will participate.

Patients must be able to understand and follow instructions and written informed consent has to be obtained. Patients are screened for eligibility according to the inclusion and exclusion criteria presented in Table 1.

**Table 1 Tab1:** Inclusion and exclusion criteria

Inclusion criteria	Exclusion criteria
• Trauma patients with surgically treated (peri)- or intra-articular fractures of the lower extremities, i.e. pelvic fractures, acetabular fractures, distal femur fractures, tibia plateau fractures, pilon fractures and foot fractures. According to the AO fracture classification type A, B, or C. • Age > = 18 years • Being able to understand the questionnaires and measurement instructions	• Restricted mobility due to other causes than the surgically treated (peri)- or intra-articular fracture, i.e. bilateral fractures, amputations, or ipsilateral significant fractures that hamper mobilization. • Severe non-fracture-related comorbidity of the lower extremity, e.g. congenital bone and tissue disorders. • No additional problem of rheumatic orthopaedic or neurological nature of the lower extremities (e.g. primary coxarthrosis or gonarthrosis) • Congenital bone and tissue disorders. • No informed consent

Participants for the intervention group, i.e. who will receive treatment according to the permissive weight bearing protocol, will be recruited in Maastricht University Medical Center (Maastricht) and in Zuyderland Medical Center (Heerlen). This intervention has already been implemented in these two hospitals, as well as in Adelante Rehabilitation Center (Hoensbroek).

The control group will be recruited in Viecuri Medical Center (Venlo), Maxima Medical Center (Veldhoven), Catharina Hospital (Eindhoven) and Elkerliek Hospital (Helmond). All participating centers are located in the Netherlands. The inclusion of the participants will start in October 2017 and will continue until September 2018.

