### Randomization process

Randomization is not considered feasible because of the nature of the two different interventions. Implementation of these different protocols includes patient instructions as well as physical therapy guidance and nursing staff participation. A mix of protocols to be used on a ward is therefore considered not optimal because of information bias.

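### Every LEFS is taken after the injury and no pre-injury function is listed, so the plan can neither show nor adjust for earlier differences between the two sets of hospitals

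*Protocol article*

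**What the plan says.** All places are in the protocol article.

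- **Allocation.** Under Randomization process: "Randomization is not considered feasible because of the nature of the two different interventions". Under Population, two hospitals supply the permissive weight bearing group and four others the controls. Of the first two it says: "This intervention has already been implemented in these two hospitals, as well as in Adelante Rehabilitation Center (Hoensbroek". Aftercare is thus set by site.
- **Who is eligible.** Table 1 admits "Trauma patients with surgically treated (peri)- or intra-articular fractures of the lower extremities", from age 18 with no upper limit. It excludes mobility restricted by other causes and severe non-fracture comorbidity of the limb. It also lists rheumatic, orthopaedic or neurological problems of the lower limb. That item is worded as a negative inside the exclusion column, but its intent is clear.
- **When the LEFS is taken.** Data collection: "Baseline measurements will be performed as soon as possible post-injury (= week 0", then "Further measurements will be taken at week 2, week 6, week 12 and week 26 post trauma". Primary outcome measures: "Score on LEFS [20] at 0, 2, 6, 12 and 26 weeks post-surgery". The first section counts from trauma, the second from surgery.
- **What else is recorded.** Demographic and medical variables lists gender, age, trauma date, fracture type, injury severity score (ISS), operation, length of stay, complications and weight bearing data. Nothing there describes function before the injury. The Fugl-Meyer, SF-36 and EQ-5D-5L also start at week 0 after surgery.
- **How case mix is handled.** Statistical analyses: "Variations in case mix between centers can influence the interpretation of outcome data". It then names age, gender, ISS and number of complications as covariates, with the list left open.

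**The concern.** Without randomisation, a fair comparison depends on measuring and adjusting for the ways in which the hospitals' patients differ. For a scale of everyday lower-limb activities, how well the patient managed those activities before the injury is an obvious candidate confounder. The plan recognises that case mix can distort the comparison, but it lists no item that captures this one.

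The week-0 LEFS cannot stand in for it, because it describes a patient who is already injured. The ISS describes the injury. Number of complications can include events after aftercare has begun, so it is no proxy for the patient's earlier state.

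At stake is the reading of the week-26 difference. If one set of hospitals treats people who functioned better beforehand, part of that advantage may appear as a treatment effect, or may hide one. The direction is unknown. The Discussion intends the result to inform nation-wide introduction. A later analysis plan cannot adjust for a variable that was never collected.

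**Working it through.** **Step 1: is there any pre-injury measure?** Set the article's lists side by side.

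| Place | LEFS or function before injury? |
|---|---|
| Data collection | No; baseline follows the injury |
| Primary outcome measures | No; first LEFS at week 0 after surgery |
| Secondary outcome measures | No; all three scales start at week 0 after surgery |
| Demographic and medical variables | No |
| Named covariates | No; age is the nearest proxy |
| Table 1 exclusions | Restrict the range, record no value |

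On either clock, trauma or surgery, all LEFS values follow the injury. This finding needs no assumption about how low the week-0 score is.

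**Step 2: the planned difference.** From Sample size calculation, the control mean is 65 (SD 10) and the increase of interest is 10%: 0.10 × 65 = 6.5 points. The article gives no figure for a pre-injury gap, so there is no plan figure on this point to reproduce.

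**Step 3: illustrative bias.** Two inputs are assumptions that are not in the document: the pre-injury gap that remains after eligibility and age adjustment (0 to 5 points), and the carry-over to week 26 (0.5 to 0.8 points per point). Bias = gap × carry-over.

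| Residual gap | Bias at 0.5 | Bias at 0.8 | Share of 6.5 |
|---|---|---|---|
| 0 | 0 | 0 | 0% |
| 3 | 1.5 | 2.4 | 23% to 37% |
| 5 | 2.5 | 4.0 | 38% to 62% |

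If the 10% is read as a share of the 80-point scale, the planned difference is 8 points and the largest entry is 4.0 / 8 = 50%.

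**Step 4: what such a bias does to the test.** Take 51 per group and SD 10 as stated, with no true effect. The standard error is 10 × √(2/51) = 1.98. The chance of two-sided p < 0.05 with bias b is Φ(b/1.98 − 1.96) + Φ(−b/1.98 − 1.96).

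| Bias (points) | 0 | 1 | 2 | 3 | 4 |
|---|---|---|---|---|---|
| Chance of p < 0.05 | 5% | 8% | 17% | 33% | 52% |

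These probabilities are conditional on the assumed bias. They do not estimate this study's error rate.

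**The case against.** **The exclusions and age adjustment already deal with it.** In part. Table 1 removes many patients with impaired function before the injury, and age is a plausible proxy for what remains. It would therefore be wrong to infer that a pre-injury gap passes undiminished into the week-26 LEFS; only the residual counts, and it could be zero. But restriction is not measurement, and patients of the same age differ.

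**A condensed article need not list every baseline item.** The flow chart is not shown, and the covariate list is openly abbreviated, so the full protocol may record more. That is a fair caution. However, the article does set out the variables to be recorded and the full LEFS schedule, and neither contains such an item. If the full protocol already collects one, all that remains is to name it as a covariate.

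**The plan never claims that the week-0 LEFS shows pre-injury equality.** Correct. It is simply the first of five measurement points. The point is that nothing else listed fills the gap.

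**Stronger readings.** A reader might infer that week-0 scores sit at the floor, so that fit and frail patients look alike. Low scores are likely just after such fractures, but the article gives no week-0 mean or spread. A reader might also infer that the week-0 score already carries the treatment, because in the permissive group "patients are instructed and trained to start weight bearing as tolerated". That is possible, but the article does not say whether baseline comes before or after the first instruction. Neither reading is established, and the conclusion needs neither.

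**The remedy has its own weaknesses.** True. Recall comes from patients who are not blinded and may know their regimen, and in a population screened for mobility the recalled scores may cluster near 80.

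**Conclusion.** The point holds in a limited form. As written, the article plans a non-randomised comparison by hospital on the LEFS with no measure of function before the injury. The week-0 LEFS cannot show or adjust for pre-injury differences. The exclusions and age adjustment reduce the resulting confounding by an unknown amount and leave the rest uncontrolled.

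Its size cannot be derived from the document. Under the stated assumptions the bias is 0 to 4 points against a planned 6.5, in either direction. The upper end, about 62% of the planned effect, needs both the largest assumed gap and the largest assumed carry-over, so it is not an expected value. This is a worthwhile and cheap improvement to data collection, but it does not show that the groups will in fact differ.

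**What to change.** 1. At the existing week-0 contact, and before the first weight bearing instruction where possible, have patients also answer the 20 LEFS items for their state before the injury.
2. Report this recalled score by group, including its spread and the share at or near 80.
3. Add it to age, gender, ISS and fracture type as a covariate in the primary comparison.
4. Keep the week-0 LEFS as the first point of the recovery curve, and do not present it as a pre-injury baseline.
5. Define week 0 and the later visits on one clock, since Data collection counts from trauma and the outcome sections from surgery. Record whether the baseline questionnaire preceded the first instruction.

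Cost: a few minutes of questionnaire, with no additional visit. Recall error in unblinded patients and a possible ceiling should be stated as limitations. The item has to be collected at enrolment, because recall obtained months later would be much weaker.

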### Demographic and medical variables

The following variables will be recorded:GenderAgeDate and time of traumaType of fractureInjury severity score (ISS)Type of operationLength of stay in hospitalComplications before rehabilitationWeight bearing policyTime between accident and weight bearingDate of 100% weight bearing (insoles)Complications during rehabilitation.

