We have developed an early permissive weight bearing post-surgery rehabilitation protocol, where progression of weight bearing is guided by the subjective experience (e.g. pain, weight bearing tolerance) of the patient and therapist, and objective parameters (e.g. temperature of the limb, edema, and gait parameters) are registered. This early permissive weight bearing protocol has previously been implemented and validated in our rehabilitation center since 2005. Follow up and evaluation of the permissive weight bearing protocol are ensured by recording and documenting weight bearing milestones (e.g. walking with 2 crutches, walking with 2 canes, walking with one cane and walking without any walking aids) in a database. Retrospective analysis of the complications that occurred while using this new protocol showed a complication rate of 10%, non-unions and infections being the most common complications. A comparison of our complication rate to data reported in literature that were based on protocols using the existing guidelines, such as the current non-weight bearing guidelines (AO protocol), showed lower complication rates for all our groups treated according to the permissive weight bearing protocol. Recent literature has reported composite postoperative complication rates of up to 37%, with an average of 10–20% in patients with lower extremity fractures [7–16].

In our study we want to compare our early permissive weight bearing protocol to the currently existing AO treatment guidelines in a prospective comparative cohort study. In addition to the follow up, featuring clinical documentation and registration of weight bearing milestones, new techniques for ambulatory measurements of loading (i.e. gait analysis by means of insoles) and non-invasive quantification of muscle mass will be used. This study will be performed in patients with (peri)- or intra-articular fractures of the pelvis/acetabulum and lower extremity after surgical treatment for which existing guidelines do not allow early full weight bearing in the first 6–12 weeks.

The primary research question is: How do the current guidelines (AO guidelines) and a permissive weight bearing protocol compare as to early recovery of functional outcome in trauma patients with fractures of the lower extremities after 6 months?

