### Hypothesis

#### Hypothesis 1

The permissive weight bearing protocol will lead to 1A: a better outcome at activity level (as measured with the Lower Extremity Functional Scale (LEFS)), 1B: a better early recovery at function level (as measured with the Brunnstrom Fugl-Meyer (BFM) test), 1C: a better participation (as measured with the SF-36) and 1D: a better quality of life (as measured with the EQ-5D-5L) in the first 6 months post-surgery, as compared to patients who are treated according to current standard guidelines. It is expected that in the long-term (i.e. 1 year) functional outcome will be similar between the treatment groups and will therefore not be the primary focus of this study [3]. We have chosen for the three scales mentioned above to cover the major outcome levels in the ICF model [17].

#### Hypothesis 2

The permissive weight bearing protocol for trauma patients with fractures of the lower extremities is more cost-effective compared to the non-weight bearing protocol and current guidelines.

#### Hypothesis 3

The rate of complications (e.g. failure of osteosynthesis, secondary displacement of fracture parts, non-union, infections) is equal or lower in patients who are treated according to the permissive weight bearing protocol compared to patients treated according to standard current guidelines.

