### Secondary outcome measures

Function (Brunnstorm Fugl-Meyer)Participation (SF-36)Improvement in quality of life (EQ-5D-5L)Reduction in health and society costs (RUM)Total complication rate

Outcome variables gauging functional outcome:Score on Brunnstrom Fugl-Meyer [21] at 0, 2, 6, 12 and 26 weeks post-surgeryScore on SF-36 [22] at 0, 2, 6, 12 and 26 weeks post-surgeryScore on EQ-5D-5L [23] at 0, 2, 6, 12 and 26 weeks post-surgery

Outcome variables gauging complication rate:Failure of the osteosynthesis, defined as loosening or breakage of implantsMigration of fracture parts, defined as > 3 mm articular step-off and/or varus/valgus malalignment > 5 degreesInfection, defined as (but not limited to) purulent wound drainage, inflammation, erythema, fever, increased white blood cell (WBC) count, increased C-reactive protein (CRP) and/or increased erythrocyte sedimentation rate (ESR), necessitating admission for intravenous antimicrobial treatment and/or revision surgeryNon-union, defined as no radiographic union achieved after 6 months or no progress in healing

Outcome variables gauging compliance [5, 6, 24–26]:Self-reported adherence to the fracture-related weight bearing protocol, will be recorded in medical records by physical therapists.Peak load (% body weight) and step duration (in seconds) as measured by the Sensistep [27] insole pressure measurement system. The Sensistep will be used by the patient only during daytime. The measurements with the Sensistep will continue until the patient has shown 100% weight bearing. The time for the latter to occur, may differ between patients.

Brunnstrom Fugl-Meyer: This is a test that evaluates the degree of synergy formation. The test consists of 55 test items that can be scored on an ordinal 3 - point scale (0–2 points). The total test consists of an examination of the upper extremity, an examination of the lower extremity and an examination of the balance. For our study we will only use the examination of the lower extremity. The maximum total score concerning the lower extremities is 34 points [21].

SF-36: This is a multi-purpose, short-form health survey with 36 questions. It yields an 8-scale profile of functional health and well-being scores, as well as psychometrics-based physical and mental health summary measures, and a preference-based health utility index. The higher the score the better the participation [22].

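### The listed variables omit smoking and diabetes or other systemic comorbidity, and leave body weight and open/closed status unclear, so case-mix adjustment of the complication comparison would be incomplete

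*Protocol article*

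**What the plan says.** In the Protocol article, Demographic and medical variables introduces its list without qualification: "The following variables will be recorded:GenderAgeDate and time of traumaType of fractureInjury severity score (ISS"). Type of operation, length of stay, complications before and during rehabilitation, and three weight-bearing items complete the twelve entries.

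Two sections tie the arm to the hospital. Randomization process states: "Randomization is not considered feasible because of the nature of the two different interventions". Population recruits the intervention group in two named hospitals and the control group in four others, and says of the former: "This intervention has already been implemented in these two hospitals".

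Statistical analyses sees the consequence ("Variations in case mix between centers can influence the interpretation of outcome data") and offers covariate adjustment as the remedy, "entering various indicators of case mix as co-variates (i.e. age, gender, ISS, number of complications, etc").

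The outcome at issue is Hypothesis 3: "The rate of complications (e.g. failure of osteosynthesis, secondary displacement of fracture parts, non-union, infections) is equal or lower" under permissive weight bearing. Background reports that, in the retrospective series under this protocol, complications ran at 10%, "non-unions and infections being the most common complications". Secondary outcome measures expresses one compliance measure relative to weight: "Peak load (% body weight) and step duration (in seconds").

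**The concern.** When each hospital supplies only one arm, any difference in patient mix between the two hospital groups enters the comparison as if it were an effect of the aftercare protocol. The plan's only protection is adjustment, and adjustment can use only what has been recorded.

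The exclusion criteria cover restricted mobility, lower-limb comorbidity, and congenital bone and tissue disorders. They do not keep out smokers, patients with diabetes or patients with open fractures, so all of these can enter either arm. That such factors bear on bone healing and infection is taken here as general clinical knowledge. The article does not say so.

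The safety conclusion is at stake. The Discussion expects the results to inform nationwide introduction. An imbalance in one direction could falsely reassure about complications, and one in the other direction could raise a false alarm.

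**Working it through.** **1. What is recorded, and what that leaves.**

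| Factor | In the recorded list? | Elsewhere in the article |
|---|---|---|
| Age, gender, fracture type, ISS, operation type | Yes | Age, gender and ISS are named as covariates |
| Smoking | No | Not mentioned |
| Diabetes or systemic comorbidity | No | Not mentioned; exclusions concern the lower limb and congenital disorders |
| Body weight | No | Implied for insole wearers by peak load in % body weight |
| Open or closed fracture | Not explicit | Fracture type is not defined on this point |

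Of the four covariates named in Statistical analyses, the number of complications is not a case-mix variable for Hypothesis 3. Unless it means only complications before rehabilitation, it is the outcome itself. That leaves age, gender and ISS, plus whatever the open-ended *etc* draws from the recorded data.

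**2. Size of the possible bias.** The article gives no prevalence, imbalance or risk ratio for these factors, so there is no figure of the plan's to reproduce. All inputs in this step are assumptions. For one binary factor with risk ratio RR, prevalence p1 in one arm and p0 in the other, and no true treatment effect:

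spurious RR = (1 + p1(RR − 1)) / (1 + p0(RR − 1))

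| p1 vs p0 | RR | Calculation | Spurious RR |
|---|---|---|---|
| 20% vs 10% | 2 | 1.20 / 1.10 | 1.09 |
| 40% vs 25% | 2 | 1.40 / 1.25 | 1.12 |
| 20% vs 10% | 3 | 1.40 / 1.20 | 1.17 |
| 30% vs 10% | 2 | 1.30 / 1.10 | 1.18 |
| 30% vs 10% | 3 | 1.60 / 1.20 | 1.33 |

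If the imbalance runs the other way, the range inverts: 1.10/1.20 = 0.92 to 1.20/1.60 = 0.75. Applied to a 10% rate, 1.09 looks like 10.9% versus 10%, and 1.33 like 13.3% versus 10%. Two factors acting independently and in the same direction would multiply, for example 1.12 × 1.33 = 1.49. That is an unfavourable case, not an expected one.

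**3. Information available for adjustment.** Sample size calculation gives 51 per group, 102 in total. Background gives average rates of 10–20%. Expected events are 102 × 0.10 = 10.2 to 102 × 0.20 = 20.4. Power to distinguish 20% from 10% with 51 per group is about 29%. At 10% in both arms, the standard error of the log risk ratio is √(2 × 0.9/(51 × 0.1)) = 0.594, so a 95% interval spans a factor of exp(1.96 × 0.594) ≈ 3.2 either side. Sampling error therefore exceeds the bias in step 2, and an ordinary regression could carry very few covariates.

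**The case against.** The strongest objection is that this is a condensed article and its list need not be complete. Background plans muscle-mass measurement and registers limb temperature and edema. Population makes hospital define the arm. Peak load needs body weight. None of these appears among the twelve items, so absence from the list does not prove that an item is not collected. This argument stands in part. It weakens the point on body weight and leaves open/closed status as a matter of definition. It helps less with smoking and systemic comorbidity: the other items are at least mentioned somewhere in the article, and these are not.

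A second objection is that the causal premise and the whole magnitude come from outside the document. That is correct, which is why the sizes are given as a range under assumptions with no stated direction.

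A third is that about 10 to 20 events on a secondary outcome cannot support many more covariates, and that hospital-level differences would remain in any case. This also stands. It limits what the fix can achieve, but recording the items would still let a reader see whether the arms differ, which is useful even where the model can do little.

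A reader might also infer that the list contains no patient-level risk factor at all, or that no later analysis could address the confounding. The document supports neither reading. Age, gender, fracture type, ISS and operation type are patient-level prognostic items. Missing factors might be retrieved from hospital records, and a bias analysis could bound what remains.

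**Conclusion.** The point holds as an incomplete adjustment set. Smoking and diabetes or other systemic comorbidity are not named for recording, body weight is not listed as a baseline covariate, and open/closed status is undefined. In a non-randomised comparison of two hospitals against four that relies on case-mix adjustment, this leaves Hypothesis 3 less adjustable than it could cheaply be.

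For a single unrecorded factor, a prevalence gap of 10 to 20 points and a risk ratio of 2 to 3 give a spurious risk ratio of about 1.1 to 1.3, or its inverse. This assumes no true effect, and neither the imbalance nor its direction can be judged from the article. At the lower end the bias is minor. At the upper end it is not negligible against the 10% and 10–20% rates that Background sets side by side. It is a worthwhile improvement to data collection, not a flaw that invalidates the study.

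**What to change.** Add to the week-0 record, for every patient and not only insole wearers: smoking status, diabetes or a comorbidity grade, height and weight, and explicit open or closed fracture. If fracture type is already meant to include open/closed status, say so.

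Report the balance of these items by arm. For the complication outcome, adjust through a propensity score or a penalised model using these pre-treatment items with age, gender, fracture type and ISS. Do not use the number of complications as a covariate for that outcome. State that differences between hospitals beyond these items remain unadjusted.

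The cost is about five items per patient that are normally in the surgical chart. Collecting them prospectively is more reliable than retrieving them later from six hospitals. The downside is more candidate covariates against few events, which is the reason for a propensity score or penalisation.
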